#### Secondary outcome.

In a secondary analysis, we will also determine if left DLPFC functional connectivity change is associated with change in craving on the OCS (n = 50). If a participant elects to undergo the optional MRI visits, they will receive structural and resting-state functional magnetic resonance imaging (rsfMRI) scans. The rsfMRI scans will be used will be used to determine if active TMS affects left DLPFC resting-state functional connectivity more than sham and if change in functional connectivity between the left DLPFC and dorsal striatum and anterior cingulate cortex (ACC) is associated with change in craving score on the OCS.

### Statistical analysis plan

#### Primary outcome analysis.

A change in craving score (Δcraving) on the OCS will be calculated between pre-TMS (week 1 timepoint) and post-TMS (week 10 timepoint) and a linear model will determine whether Δcraving significantly differs between active and sham conditions (controlling for age, sex, and pre-TMS craving). Change in number of days of use on the TLFB (Δuse) will be calculated between pre-TMS (week 1 timepoint) and post-TMS (week 10 timepoint) and a model will determine whether Δuse significantly differs between active and sham conditions (controlling for age, sex, and pre-TMS days of use). In post hoc analyses, we will investigate the effects of buprenorphine dose in response to TMS.

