### Sample size

We plan to recruit up to 60 participants at each site (VUMC and SynpaticPSYCH) to obtain a completion sample of n = 50 at each site for a total of n = 100. With 80% power, a type 1 error rate of 5%, and 100 subjects across all sites, we can detect effect sizes larger than 0.40. Based on these calculations, our proposed total sample of n = 100 will provide adequate power to detect changes in craving and opioid use.

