### Randomization and blinding procedures

Randomization will be stratified by site, with independent allocation sequences generated within each site. Within each stratum, treatment assignments will be generated using a permuted block design to maintain balance between groups throughout enrollment. The study biostatistician (SV) will generate the randomization sequence. As this is a single-blind study, study personnel responsible for administering TMS will have access to the allocation sequence, maintained on a central electronic document, and will not be blinded to treatment assignment. Participants will remain blinded to the intervention they receive throughout the duration of the study. Sham (placebo) stimulation will be delivered by flipping the coil 180 degrees so that the procedure mimics the look and sound of active stimulation but deliver no stimulation to the participant. Participants will only be un-blinded if an adverse reaction to active TMS occurs and the participant can no longer remain enrolled in the study. We will make numerous attempts to retain participants in the study with phone calls, emails, and text messages.

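### Randomisation is stratified by site, but neither primary model lists site as a covariate; if site is prognostic, the test is mildly conservative and some power is forgone

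*Protocol article*

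**What the plan says.** Under Randomization and blinding procedures, the article states: "Randomization will be stratified by site, with independent allocation sequences generated within each site". Within each site, "treatment assignments will be generated using a permuted block design to maintain balance between groups throughout enrollment". Site is the only stratification factor named.

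Under Primary outcome analysis, the craving model tests whether the change from week 1 to week 10 "significantly differs between active and sham conditions (controlling for age, sex, and pre-TMS craving". The model for change in days of opioid use is described in the same way, "controlling for age, sex, and pre-TMS days of use". The first is called a linear model; the type of the second is not given. Site is in neither list, and no reason is offered for leaving it out. The sections on sample size, secondary analysis and missing data do not bring it in either.

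Under Sample size, the plan is "to obtain a completion sample of n = 50 at each site for a total of n = 100".

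**The concern.** Stratified permuted blocks balance the arms within each site, so a difference in outcome level between sites largely cancels out of the treatment contrast. The actual sampling variance of the estimate is then smaller than it would be without stratification. A model without site does not know this. It leaves the between-site variation in the residual and reports a standard error for a noisier design than the one that was run. The p-value is then too large on average and the confidence interval too wide.

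This is more than detail left to an analysis plan that is not shown, because the article names the covariates of each primary model one by one. A site effect is also plausible. Study setting describes one academic institution and one private psychiatric clinic, and iTBS equipment gives a different stimulator model for each. The Discussion argues for the private clinic on the ground that academic centres may not represent where most patients are treated.

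What is at stake is precision, in a trial that has little to spare.

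**Working it through.** **1. The plan's own figure.** The article says: "With 80% power, a type 1 error rate of 5%, and 100 subjects across all sites, we can detect effect sizes larger than 0.40". For two arms of 50 (1:1 allocation and a two-sided test assumed, as neither is stated), the detectable standardised difference is (1.960 + 0.842) × √(2/50) = 2.802 × 0.2 = 0.560, or 0.566 with the t distribution. The stated 0.40 is not reproduced by this comparison. It would need an assumption that is not given, for example covariates correlated about 0.70 with the outcome: √(1 − (0.40/0.560)²) = 0.70. That is a separate matter. Here, 0.566 serves only as the effect at which a model without a site effect has 80% power.

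**2. Inputs.** 100 completers, 50 per site (Sample size). Assumed: 25 per arm per site, and a residual gap g between site means after age, sex and baseline, in within-site SD, of 0.3, 0.5 or 0.8. The article gives no value for g.

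**3. Standard error.** With site in the model, the SE is √(4/100) = 0.200 within-site SD. Without site, the site sum of squares, 100 × (g/2)² = 25g², is added to the residual, which has about 98 degrees of freedom. Reported SE divided by correct SE ≈ √(1 + 25g²/98):
- g = 0.3: √1.0230 = 1.011
- g = 0.5: √1.0638 = 1.031
- g = 0.8: √1.1633 = 1.079

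**4. Type I error without site.** 2 × [1 − Φ(1.960 × ratio)] gives 4.7%, 4.3% and 3.5%.

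**5. Power without site.** With d in within-site SD, d/SE = 0.566/0.200 = 2.83 and the critical t is 1.984. Power ≈ Φ(2.83 − 1.984 × ratio):
- ratio 1.000 (no site effect): Φ(0.846) = 80.1%
- ratio 1.011: Φ(0.823) = 79.5%
- ratio 1.031: Φ(0.784) = 78.3%
- ratio 1.079: Φ(0.690) = 75.5%

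**6. Check by simulation** (40,000 trials, 25 per arm per site):

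| Residual site gap (SD) | SE too wide by | Type I error without site | Power without site | Power with site |
|---|---|---|---|---|
| 0.3 | 1.1% | 4.7% | 79.6% | about 80% |
| 0.5 | 3.1% | 4.5% | about 78% | about 80% |
| 0.8 | 7.9% | 3.4% | about 75% | about 80% |

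**7. Check with the planned covariates and another scale.** A second simulation (8,000 trials per setting, blocks of 4 assumed) fitted age, sex and baseline, and set the share R² of the remaining variance that site explains. Here d = 0.56 is in units of an SD that includes the site variation.
- R² = 0: power 78.6% without site, 78.5% with it.
- R² = 0.10: mean reported SE without site 0.203, against an actual SD of the estimate of 0.191 to 0.195; type I error 3.9%; power 79.3% without site, 81.9% with it.
- R² = 0.20: 0.203 against 0.182 to 0.185; type I error 3.1%; power 80.4% without site, 86.4% with it.

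The two scales are linked by R² = (g²/4)/(1 + g²/4), so gaps of 0.3, 0.5 and 0.8 correspond to R² of 0.022, 0.059 and 0.138.

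**The case against.** The loss is conditional. If site predicts nothing once age, sex and baseline are in the model, nothing is lost. The baseline value will absorb part of any difference in severity between sites, so the larger gaps may be pessimistic. One set of eligibility criteria is given for the trial, both sites use the same coil, and intensity is set from each participant's own motor threshold at every visit, so the different stimulator model is weak evidence of a site effect. All of this stands. It limits the size of the loss but gives no reason to omit site.

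A second objection concerns scale. If the effect is expressed in an SD that includes site variation, power without site does not drop below its no-site-effect level, and the omission only forgoes a gain. This is also right, and it is why the standardiser is stated with the figures. On either scale the model with site has the higher power when site matters.

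Some stronger readings are tempting but unsupported:
- A reader might infer that the standard errors are certainly too wide. The article gives no site effect, so only the conditional statement can be made.
- A reader might infer that stratifying was wasted. It was not: balance still lowers the true variance of the estimate, and only the reported standard error fails to credit it.
- A reader might infer bias or a raised false-positive rate. In the linear model the error runs the other way, against finding an effect.

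**Conclusion.** The concern holds in conditional form. The design stratifies by site, and the stated primary models ignore it. For the linear craving model the consequence is a mildly conservative test. At residual gaps of 0.3 to 0.5 SD the cost is about half a point to two points of power, rising to about five points at 0.8 SD. This is a matter of efficiency, not validity.

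The figures assume 1:1 allocation, a two-sided 5% test and 25 completers per arm per site. The plan is "We plan to recruit up to 60 participants at each site", so losses that differ by site and arm could disturb that balance among those analysed; adjusting for site would guard against this too.

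The figures should not be carried over to days of use. The same covariate is missing there, but the article says only that a model will be fitted, so the size of the loss cannot be computed.

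Nor does the omission account for the detectable effect of 0.40. To move 0.56 to 0.40, site would have to explain about 1 − (0.40/0.56)² = 49% of the residual variance.

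**What to change.** Add site as a fixed covariate to both primary models under Primary outcome analysis: change in craving, and change in days of use. It costs one degree of freedom and, by the simulation above, essentially no power if site turns out not to matter. Recruitment is projected to run to June 2028, so the term can be specified well before the outcome data are analysed.

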#### Secondary outcome analysis.

As a secondary aim, we will investigate effects of TMS on left DLPFC resting-state functional connectivity. We will perform analyses to determine: 1) if there is an effect of TMS intervention (active vs. sham) on DLPFC-striatum connectivity and DLPFC-ACC connectivity; and 2) if change in DLPFC functional connectivity (post-pre) is associated with change in craving measured using the Opioid Craving Scale (n = 50).

We hypothesize that active DLPFC-targeted iTBS will increase left DLPFC resting-state functional connectivity to the ACC and striatum. Left DLPFC-striatum connectivity will be calculated by extracting the BOLD time courses from a seed placed in the left DLPFC and masks of the striatum and ACC, calculating the Pearson correlation coefficient between the left DLPFC and these regions, then Fisher’s z-transforming the correlation estimate to generate metrics of DLPFC-striatum connectivity and DLPFC-ACC connectivity. We will fit a linear model using Δfunctional connectivity (post-pre) as the outcome and TMS intervention (active vs. sham) as the predictor, controlling for age, sex, and pre-TMS connectivity.

We also hypothesize that increased left DLPFC resting-state functional connectivity will be associated with reduced craving on the OCS. To test this, we will fit a linear model using Δcraving (post-pre) as the outcome and Δfunctional connectivity as the predictor, controlling for pre-TMS craving, pre-TMS functional connectivity, age, and sex.

We will also perform brainwide seed to voxel analyses of left DLPFC resting-state functional connectivity to determine alternative regions where active TMS changed connectivity more than sham and to identify alternative regions where ΔDLPFC functional connectivity was associated with Δcraving.

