Is TMS for OUD effective, and if so, how does it exert its effects? Only one study of TMS for OUD has included neuroimaging [24], despite neuroimaging being critical for helping to characterize the neural circuit changes that occur with TMS treatment.Is a weekly dosing schedule of TMS for OUD a feasible and acceptable adjunctive treatment? A previous study [26] testing therapeutic TMS protocols (i.e., daily sessions of treatment over multiple weeks) struggled with recruitment and retention, questioning the feasibility and acceptability of this intervention for this population.Can we provide TMS for populations with OUD beyond urban academic medical centers? Expanding access to TMS has been a challenge for the field more broadly, besides the treatment of SUDs. While clinical trials for TMS are typically conducted in academic medical centers, more widespread clinical application would ultimately require delivery of TMS for SUDs in private outpatient clinics nationwide.

To address these questions, we designed a multi-site randomized controlled trial of TMS for OUD among individuals receiving buprenorphine treatment. We will implement a novel weekly stimulation protocol designed to improve treatment efficiency and better align TMS delivery with routine weekly clinic visits. The trial will be conducted across both an academic medical center and private practice clinics throughout Tennessee to help address the question of clinical applicability beyond academic medical settings. Our central hypothesis is that DLPFC-targeted iTBS will significantly reduce both opioid craving and opioid use. In secondary analyses, we will use neuroimaging (MRI) to assess whether a change in functional connectivity between the DLPFC and both the dorsal striatum and anterior cingulate cortex (ACC) is associated with reductions in craving. Ultimately, this work aims to establish a safe and effective adjunctive therapy to directly mitigate the severe craving and high relapse rates that limit current OUD treatments.

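### The secondary model relating connectivity change to craving change pools both arms without a treatment term, so its coefficient describes an association but does not support the mechanistic reading

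*Protocol article*

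**What the plan says.** The Secondary outcome analysis section of the Protocol article sets out two region-based models for the MRI subset.

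- **Treatment and connectivity.** Change in connectivity is the outcome, with "TMS intervention (active vs. sham) as the predictor, controlling for age, sex, and pre-TMS connectivity". Arm is in this model.
- **Connectivity and craving.** This model tests whether higher connectivity goes with lower craving: "we will fit a linear model using Δcraving (post-pre) as the outcome and Δfunctional connectivity as the predictor". Its adjustment set is then listed in full and holds four items, namely the two baseline values and two demographic variables: "controlling for pre-TMS craving, pre-TMS functional connectivity, age, and sex". Arm is not in this model.

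The sample for the second model is given as 50, which is the imaging subset, and nothing limits it to the active arm. The section describes no arm-by-connectivity interaction, within-arm slope or mediation analysis. It does add a brainwide seed-to-voxel analysis that also relates connectivity change to craving change; its covariates are not listed.

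The protocol expects treatment to move both variables. On connectivity: "active DLPFC-targeted iTBS will increase left DLPFC resting-state functional connectivity to the ACC and striatum". On craving, in the Introduction: "Our central hypothesis is that DLPFC-targeted iTBS will significantly reduce both opioid craving and opioid use". The Abstract (Aims and Discussion), the Discussion and the Conclusion all present the imaging work as informing how TMS changes craving.

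**The concern.** Under the protocol's own hypotheses, arm causes a shift in the predictor and a shift in the outcome. A regression that pools the arms and leaves arm out attributes part of the between-arm difference in craving to connectivity. A significant coefficient could then reflect a circuit-craving link, two parallel effects of treatment, or a mixture.

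The craving effect need not come from stimulation. The Randomization and blinding procedures section describes a sham made by flipping the coil, which delivers no stimulation, and operators who know the allocation. If expectation lowered self-reported craving in the active arm while stimulation separately changed connectivity, the pooled model could still return an association in the expected direction.

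What is at stake is the secondary, mechanistic conclusion. The primary comparisons of craving and opioid use are not affected.

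**Working it through.** **The plan's own figure.** The protocol gives no power or effect size for this model, so there is nothing to reproduce. The only effect size it states is 0.40, in the Sample size section, for craving and opioid use with 100 participants.

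**Inputs from the protocol.** n = 50; covariates pre-TMS craving, pre-TMS connectivity, age and sex; 5% type 1 error (stated for the primary analysis, and taken two-sided here).

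**Assumptions.** A 25:25 split (the allocation ratio is not stated). Arm effects of size d_c (reduction in craving) and d_f (increase in connectivity), in within-arm SDs after baseline adjustment. The range runs from 0.4, the protocol's one figure read as an SD unit, to 1.0. Within-arm association is set to zero.

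**Step 1: induced correlation.** With equal arms, arm adds d_c²/4 and d_f²/4 to the two variances and d_c·d_f/4 to the size of the covariance. So

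|r| = (d_c·d_f/4) / √[(1 + d_c²/4)(1 + d_f²/4)]

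- 0.4/0.4: 0.04 / 1.04 = 0.04
- 0.4/0.8: 0.08 / √(1.04 × 1.16) = 0.07
- 0.8/0.8: 0.16 / 1.16 = 0.14
- 1.0/1.0: 0.25 / 1.25 = 0.20

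The sign is negative (more connectivity, less craving), which is the hypothesised direction.

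**Step 2: rejection rates.** These come from 8,000 simulated trials per scenario, testing the connectivity-change coefficient two-sided at 5%. The Monte Carlo standard error near 5% is √(0.05 × 0.95 / 8,000) = 0.24 percentage points.

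| d_c / d_f | Without arm | Without arm, hypothesised direction (nominal 2.5%) | With arm |
|---|---|---|---|
| 0.4 / 0.4 | 6.2% | 4.6% | 5.4% |
| 0.4 / 0.8 | 8.1% | 7.2% | 5.0% |
| 0.8 / 0.8 | 15.0% | 14.9% | 5.3% |
| 1.0 / 1.0 | 27.0% | 26.9% | 4.7% |

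**Step 3: when it vanishes and when it grows.** With an effect on craving only (0.4/0) the rate without arm is 5.1%; with an effect on connectivity only (0/0.8) it is 4.5%. Both are at the nominal level. A larger sample does not help: at n = 100 the rates without arm are 11.0% (0.4/0.8) and 26.1% (0.8/0.8).

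**Step 4: price of adjustment.** The planned model has 50 − 6 = 44 residual degrees of freedom; with arm it has 43. The share of connectivity-change variance that lies between arms, and that adjustment removes, is (d_f²/4)/(1 + d_f²/4): 0.16/1.16 = 14% at 0.8 SD and 0.25/1.25 = 20% at 1.0 SD.

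**The case against.** The strongest reply is that the plan hypothesises an association, and in every scenario with two non-zero arm effects a pooled association does exist. Rejecting is then correct for the question as worded: "change in functional connectivity between the left DLPFC and dorsal striatum and anterior cingulate cortex (ACC) is associated with change in craving score". This stands. The rates above are error rates only if the result is read as a link within arms, that is, as mechanism. Some of the article's mechanistic language is also hedged. But the Abstract's secondary aim is about craving changes related to iTBS, and the Conclusion promises insight into neural mechanisms, so that reading is the one intended.

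A second reply is that the marked inflation needs large effects on both variables, which the protocol does not claim. This also stands: at 0.4/0.4 and 0.4/0.8 the excess is one to three percentage points. The planned tests of arm on craving and arm on connectivity would also help show whether the condition is met.

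A third is that the covariates could be settled in a fuller document. That is weak here, because the list is printed in full and the neighbouring model does name arm.

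Finally, adjusting for arm does not prove mediation. The adjusted coefficient is still an observational association between two post-randomisation changes. This is right and limits what the fix can claim.

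**Conclusion.** The point holds as a limit on interpretation. The pooled coefficient describes an association across the trial sample; it cannot by itself separate a circuit-craving link from two parallel arm effects. The excess over 5% is small at moderate arm effects (about 6% to 8%) and marked when both are large (15% to 27%). These figures rest on assumed effects, a 25:25 split and zero within-arm association.

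Three stronger readings are not supported.

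- A reader might infer that false positives rise whenever the treatment works better. They rise only if arm affects both variables; a strong craving effect with no connectivity effect causes none.
- A reader might infer that this regression is the only test linking circuit change to craving change. The same section also plans the seed-to-voxel analysis.
- A reader might infer from "a seed placed in the left DLPFC and masks of the striatum and ACC" that a region other than the dorsal striatum will be tested. The Secondary outcome section names the dorsal striatum, so the shorter term is most naturally shorthand, and a condensed article commonly leaves mask definitions to the full protocol.

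**What to change.** 1. Add treatment arm as a main effect to the model of craving change on connectivity change, keeping the listed covariates.
2. Include arm likewise in the seed-to-voxel analysis of craving change.
3. Report the arm-by-connectivity-change interaction as exploratory.
4. Base any mechanistic statement on the arm-adjusted coefficient, and describe it as consistent with mediation, not proof of it.
5. If the pooled model is kept, label it descriptive.

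The cost is one residual degree of freedom (44 to 43) and some loss of predictor variance, about 14% if the connectivity effect is 0.8 SD. No new data are needed. The Study status and timeline section projects recruitment to June 2028, so the change can be specified well before analysis.

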### Data retention and missing data

We will collect data from all participants who attend visits. If missingness in outcome or covariate values are greater than 10%, we will perform multiple imputation by chained equations using 100 resampled datasets for the primary outcome analyses and secondary analyses that do not use full image outcome variables [31,32]. We will compare results with and without multiple imputation as supplementary analyses. For full image analyses, we will use complete-case analysis. If a participant deviates from the protocol, we will perform sensitivity analyses using data collected per-protocol and including those who deviated from the protocol in separate analyses.

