### Outcomes and assessments

#### Primary outcome.

The primary outcome is to determine the effects of active left DLPFC targeted iTBS compared to sham on craving and opioid use in 100 people with OUD. Specifically, this study seeks to provide evidence that L DLPFC-targeted iTBS leads to reduced craving and opioid use in individuals with OUD.

Participants’ craving and drug use will be assessed prior to receiving iTBS, during iTBS intervention and following the end of iTBS (10, 12 and 20 weeks). Craving will be measured using the Visual Analogue Scale (VAS) on the Opioid Craving Scale (OCS). Opioid use will be measured as the number of days of use in the preceding week using the Timeline Follow Back (TLFB).

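### The primary craving model leaves out the in-treatment scores, and multiple imputation is used only if missingness passes 10%, so no single primary missing-data method is fixed

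*Protocol article*

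**What the plan says.** All references are to the protocol article.

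- **Primary outcome analysis.** The craving change score "will be calculated between pre-TMS (week 1 timepoint) and post-TMS (week 10 timepoint) and a linear model will determine whether" it differs between arms, "controlling for age, sex, and pre-TMS craving". No visit between weeks 1 and 10 enters this model. The change in days of opioid use is taken over the same two time points.
- **Primary outcome.** Craving and drug use are "assessed prior to receiving iTBS, during iTBS intervention and following the end of iTBS", the last at weeks 10, 12 and 20. The Study design section adds that questionnaires on substance use and psychiatric symptoms are completed at each of the eight TMS visits.
- **Data retention and missing data.** "If missingness in outcome or covariate values are greater than 10%, we will perform multiple imputation by chained equations". The rule specifies 100 imputed datasets and covers the primary analyses as well as the secondary ones, apart from those on full-image outcomes. It continues: "We will compare results with and without multiple imputation as supplementary analyses". No method is named for missingness of 10% or less, and the variables in the imputation model are not listed.
- **Sample size.** Up to 60 participants are recruited per site "to obtain a completion sample of n = 50 at each site for a total of n = 100".

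**The concern.** Two features combine. First, the primary model looks only at weeks 1 and 10. A participant who attends for seven weeks and then leaves has a visible craving course, but when the model is run complete-case that person contributes nothing. Second, whether the model is complete-case or imputed is decided by how much data turn out to be missing, so the primary method is not known until the data are in.

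The 10% line does not track the problem. Bias depends on who leaves and on whether the analysis uses what was known about them before they left. Imputing week-10 craving from only baseline craving, age and sex adds almost no information about a dropout beyond what the complete-case model already conditions on. Crossing the threshold therefore changes the method without necessarily changing the answer.

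At stake is an understated treatment effect if people with rising craving leave the sham arm more often: the sham participants still present at week 10 would then look better than the sham group as a whole.

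**Working it through.** **1. Which branch is expected?** Enrolment is 120 and the completer target is 100, so the implied loss is 20/120 = 16.7%. The inflation reproduces: 100/(1 - 1/6) = 120. More than 10% of 120 means 13 or more missing. Treating week-10 missingness as binomial with n = 120, the chance that the trigger fires is:

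| True missing rate | P(13 or more of 120 missing) |
|---|---|
| 5% | 0.01 |
| 8% | 0.16 |
| 10% | 0.42 |
| 12% | 0.69 |
| 16.7% | 0.97 |

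On the plan's own allowance, imputation is the expected branch. With better retention, at about 8% to 12%, the choice of method is close to a matter of chance.

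**2. Does the branch matter, or the information used?** This was checked by simulation, 2,000 trials per scenario. All settings below are assumptions, except the total of 120 and the value 0.40, which is the plan's detectable effect size read here in SD units.

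- 60 per arm; a true effect of -0.40 SD at week 10, building linearly from week 1.
- Scores at weeks 1 to 8 and 10 have unit variance. The correlation between two visits d weeks apart is 0.5 + 0.5 × 0.7^(d/2). This gives 0.5 + 0.5 × 0.7^4.5 = 0.60 for weeks 1 and 10, and 0.5 + 0.5 × 0.7 = 0.85 for weeks 8 and 10.
- The chance of leaving before each visit is logistic in the last observed score, with slope 1 in sham and slope 0 in active ("sham only") or slope 1 in both arms ("both"). The intercept sets the overall loss.
- Each analysis regresses week-10 score on arm and baseline. With baseline in the model, the arm effect is the same as for the change score. Imputation was by regression within arm, which shows the expected point estimate; imputation variance was not pooled, so no power is claimed.

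| Craving drives dropout in | Mean missing | Full data | Complete-case | Imputed, baseline only | Imputed, weekly scores |
|---|---|---|---|---|---|
| Sham only | 6.7% | -0.398 | -0.378 | -0.378 | -0.397 |
| Sham only | 13.7% | -0.402 | -0.364 | -0.363 | -0.402 |
| Sham only | 30.6% | -0.405 | -0.320 | -0.314 | -0.404 |
| Both | 15.1% | -0.401 | -0.391 | -0.390 | -0.397 |

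The estimates vary between simulated trials with an SD of about 0.16 in the 7% to 15% rows, so the simulation error of a mean is about 0.16/√2000 = 0.004.

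**3. Reading the table.** Complete-case and baseline-only imputation agree within 0.006 in every row. The trigger alone therefore recovers nothing; the weekly scores do. The shortfall is about 0.02 SD below the trigger (7% missing), 0.04 SD at 14% and 0.08 SD at 31%. At 14% that is 0.04/0.16, a quarter of the estimate's standard deviation.

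**The case against.** Baseline-adjusted analysis at one prespecified time point, with multiple imputation, is a standard primary analysis. The threshold is set in advance and depends on the amount of missing data, not on the treatment effect. Results with and without imputation will both be shown, so any influence of the switch will be visible. A condensed article may leave the list of imputation variables to a full analysis plan. Below the trigger the simulated bias is only 0.02 SD.

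Much of this stands, and it rules out several stronger readings that a reader might infer:

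- **That dropouts' in-treatment scores are discarded as a rule.** The article does not say so. Above 10%, dropouts are retained through imputation, and the scores are neither included nor excluded. Only the complete-case branch loses them for certain.
- **That study dropout will differ by arm.** The Aims predict higher treatment retention under active iTBS, and the Introduction reports buprenorphine discontinuation. Neither is attendance at study visits. Dropout related to both arm and craving is plausible, but it is an assumption here.
- **That the switch inflates type I error.** Nothing in the article or in this check shows that.
- **That the Opioid Craving Scale is certainly given every week.** This is inferred from the Study design and Primary outcome sections; the schedule figure is not shown.

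What the objection does not answer is the stated rule itself. The article fixes a trigger that picks the primary method from the observed missingness, and a supplementary comparison does not say which of two differing results is the trial's answer.

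**Conclusion.** The point holds as a weakness in a stated rule. The primary model omits the in-treatment craving scores, is complete-case by default at 10% missingness or less, and switches method above that without a commitment to use those scores. It should be corrected, but it does not invalidate the trial.

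The size is modest and conditional. With craving-driven loss confined to sham, the understatement is about 5% of a 0.40 SD effect at 7% missing (0.02/0.40) and about 10% at 14% missing (0.04/0.40). With equal craving-driven loss in both arms it is about 0.01 SD. These figures rest on the assumed correlations and dropout model, and on dropout depending on scores already observed. If dropout depends on craving after the last visit, the weekly scores would help only in part.

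**What to change.** Delete the 10% trigger and prespecify one primary method for all randomised participants, whatever the missingness. Either route keeps the week-10 comparison:

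1. **Imputation always.** Run chained-equation imputation separately by arm, with the in-treatment craving and opioid-use scores as auxiliary variables, then fit the planned week-10 baseline-adjusted model. This is the smaller change to the text.
2. **Repeated-measures model.** Model the post-baseline visits with arm by visit, and take the week-10 contrast as primary. Week-1 craving enters as a covariate only, not also as a modelled visit. Name one covariance structure and an ordered fallback. If all post-baseline visits are used (weeks 2 to 8, 10, 12 and 20), an unstructured matrix has 10 × 11/2 = 55 parameters for at most 120 people, so the fallback order matters.

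Keep complete-case as a sensitivity analysis. Confirm against the schedule figure that the craving scale is collected at each TMS visit; if it is collected less often, use the visits that exist.

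The cost is some analysis wording and code, and an imputation or covariance model that must be written down in advance. Visits, sample size and data collection do not change. Recruitment is projected to run to June 2028, so the change can be made before outcomes are analysed.
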